### Objectives {7}

To implement CGA for frail older adults aged 75 years and over, which will be provided by the SOLAR team including a senior geriatric specialist registrar, senior physiotherapist, senior occupational therapist, senior medical social worker and senior pharmacist in the Emergency Department and Acute Medical Assessment Unit (AMAU) in a University teaching hospital.To examine if early assessment and intervention by the SOLAR team improves the quality, safety and cost-effectiveness of care among frail older adults who present to the ED and AMAU.To conduct a process evaluation of the CGA intervention through focus group interviews with the SOLAR team, representatives from the wider ED and AMAU staff along with patient representatives regarding the feasibility, acceptability, and delivery of the intervention.

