### Outcomes{12}

The primary outcome of the study is patient ED length of stay or Patient Experience Time (PET) time, which is recorded as time of arrival at the ED until discharge from ED to home or admission to a ward. For participants in the AMAU, this is defined as the time from arrival at the hospital to discharge from AMAU or admission to a medical ward.

Secondary outcomes include mortality, ED revisit, unplanned hospital visit(s) or nursing home admission within 30 days and 6 months of initial index visit. Healthcare utilisation will also be captured at 30 days (GP visit, Public Health Nurse visit, Allied Health Services) by telephone contact. Follow-up at 30 days and 6 months will be captured by telephone contact by a research nurse who is blinded to group allocation. Patient reported outcomes at 30 days include a global measure of function (Barthel Index) and quality of life survey (EuroQoL-5D EQ-5D) [13, 14]. In addition, patient satisfaction with their index visit will be explored using a patient satisfaction questionnaire. A detailed process evaluation will be completed using a mixed methods approach. The process evaluation will explore stakeholders’ experience of implementing the intervention as well as examining factors that enabled or hindered the delivery of same.

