### Sample size {14}

We estimated the sample size based on the primary outcome (ED length of stay) using G*Power version 3.1. Using data from the Patient Experience Time (PET) database employed in the ED at UHL (unpublished data), the average ED length of stay for patients aged 75 and older for the 2019 yearly period was 18.63 h (standard deviation 19.91 h). Estimating a 50% decrease in ED length of stay in the intervention group (mean 9.31 h), and with a 20% attrition rate to follow-up, a sample size of 236 patients (118 in each group) will be required to achieve 90% power with two-tailed tests at an alpha level of 0.05.

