## Statistical methods

### Statistical methods for primary and secondary outcomes {20a}

Appropriate descriptive statistics will be used to describe the baseline characteristics of study participants. These will include proportions, percentages, ranges, means and standard deviations and medians and interquartile ranges (where data are not normally distributed). We will analyse differences across the two groups for all continuous outcomes (ED length of stay, etc.) by using independent samples *t* tests with 95% confidence intervals. The non-parametric equivalent, the Mann-Whitney test, will be used for skewed data.

Incidence of ED return, unplanned hospital admission, nursing home admission and healthcare utilisation will be explored using crude and adjusted risk ratios with associated 95% confidence intervals using logistic regression. Unit costs will also be applied to resource use data. The total costs of health and social care input will be compared between groups with complete resource utilisation data, using non-parametric bootstrapping (it is anticipated that the data will be highly skewed in terms of distribution). A 5% level of statistical significance will be used throughout the analyses.

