### Methods for additional analyses (e.g. subgroup analyses) {20b}

There will a subgroup analysis based on discharge location and Clinical Frailty Score [16].

Subgroup analysis exploring the subgroup of control participants who were seen by the OPTIMEND team will be carried out. OPTIMEND is a health and social care professional team who perform certain components of CGA but without specialist geriatric medicine input.

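### A flat 5% significance level covers about 14 unranked secondary comparisons, and nothing says what a significant result on one of them may be used to claim

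*Protocol article*

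**What the plan says.** All references are to the protocol article.

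- **Primary outcome.** Outcomes {12} names one: time in the ED, or the equivalent time for patients in the Acute Medical Assessment Unit. Sample size {14} powers the trial on it alone.
- **Secondary outcomes.** The same section continues: "Secondary outcomes include mortality, ED revisit, unplanned hospital visit(s) or nursing home admission within 30 days and 6 months of initial index visit". It adds three kinds of healthcare use at 30 days, the Barthel Index and EQ-5D at 30 days, and patient satisfaction.
- **Analysis.** Statistical methods {20a} says that ED return, unplanned admission, nursing home admission and healthcare use "will be explored using crude and adjusted risk ratios with associated 95% confidence intervals". It also plans a between-group comparison of total costs. The paragraph then closes with "A 5% level of statistical significance will be used throughout the analyses".
- **Subgroups.** Additional analyses {20b} says "There will a subgroup analysis based on discharge location and Clinical Frailty Score", and adds a further subgroup of control patients seen by the OPTIMEND team. Neither the outcomes nor the number of tests is given.
- **Aim.** Objectives {7} asks whether the team "improves the quality, safety and cost-effectiveness of care among frail older adults who present to the ED and AMAU".

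No section ranks the secondary outcomes, divides the error rate between them, names a key secondary or limits claims to length of stay.

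**The concern.** The closing sentence of {20a} is a stated rule, in a section whose heading covers primary and secondary outcomes alike. Read naturally, it gives each secondary comparison its own 5% test.

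This matters here because of the gap between the aim and the primary outcome. Time in the department says little about safety, function, quality of life or return to hospital. Any conclusion on those questions has to come from the secondary outcomes, and for them the article sets no limit on what a single p < 0.05 may be taken to show. With many such tests, an isolated significant result can easily arise by chance.

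**Working it through.** **The plan's own figure.** The article gives no error rate for the family of secondary tests. Its one related figure is the sample size: 236 in total, 118 per arm, for 90% power at a two-sided 5% level. From a mean of 18.63 h, a target of 9.31 h and an SD of 19.91 h, the standardised difference is (18.63 − 9.31)/19.91 = 0.468. A two-sided t test with 90% power then needs 97 per arm. For 20% attrition, 97 × 1.2 = 116.4 gives 117 per arm (234 in total), while 97/0.8 = 121.25 gives 122 per arm (244). The stated 236 is close to the first. It concerns only the primary outcome and does not bear on the secondaries.

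**Counting the secondary comparisons (Outcomes {12}).**

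| Group | Comparisons |
|---|---|
| Death, ED revisit, unplanned hospital visit, nursing home admission, each at 30 days and 6 months | 4 × 2 = 8 |
| GP, public health nurse and allied health use at 30 days | 3 |
| Barthel Index and EQ-5D at 30 days | 2 |
| Satisfaction | 1 |
| **Total** | **14** |

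The cost comparison in {20a} would make 15. The Abstract also places function and quality of life at 180 days, which would make 16, or 17 with costs. Subgroup tests cannot be counted. Crude and adjusted versions of one risk ratio are not counted separately, since they would usually be highly correlated.

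**Independent tests, all null, each at two-sided 5%.**

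- Any false significant result: 1 − 0.95^k. For k = 14 this is 51.2%; for k = 17, 58.2%.
- A false result favouring CGA: 1 − 0.975^k. For k = 14 this is 29.8%; for k = 17, 35.0%.
- Expected false results among 14: 14 × 0.05 = 0.70 in either direction, and 14 × 0.025 = 0.35 favouring CGA.

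**Correlated tests.** The article gives no correlations, so a range is assumed. The figures come from simulating 14 null test statistics with a common positive correlation, each outcome oriented so that higher means better.

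| Assumed correlation | Either direction | Favouring CGA |
|---|---|---|
| 0 | 51% | 30% |
| 0.1 | 50% | 27% |
| 0.3 | 44% | 22% |
| 0.5 | 35% | 17% |
| 0.7 | 25% | 12% |
| 0.8 | 20% | not computed |

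If instead the two time points of one outcome correlate at 0.7 and different outcomes at 0.2, the either-direction rate is 45%. The eight event comparisons alone give 34% if independent, 25% at correlation 0.5 and 16% at 0.8.

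**Which outcomes carry exploratory wording.** In {20a} the verb covers ED return, unplanned admission and nursing home admission (3 × 2 = 6 comparisons) and healthcare use (3). In {12} it covers satisfaction (1). That is 10 of 14. Mortality (2), Barthel (1) and EQ-5D (1) do not carry it, nor does the cost comparison. For those four alone, 1 − 0.95^4 = 19% in either direction and 1 − 0.975^4 = 10% favouring CGA, if independent.

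**The case against.** **A single primary outcome already gives a hierarchy.** This stands in part. Secondary tests do not inflate the 5% error of the length-of-stay test, and leaving secondaries unadjusted below one primary outcome is common. What is missing is any order or status among the secondaries themselves.

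**Most secondaries are described as explored.** This is true of 10 of the 14, and the OPTIMEND subgroup is worded similarly. It would be wrong to say that the article has no exploratory language. But the verb misses mortality, Barthel, EQ-5D and costs, and the same paragraph then applies a significance threshold to everything. That falls short of a designation.

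**Multiplicity belongs in the analysis plan, which is not shown.** Silence in the article would be no fault. The point rests instead on what the article does state. An analysis plan that limits secondary claims would need to be reconciled with that sentence. The sentence does not itself say that the level is per test, so this is its natural reading rather than its explicit content.

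**The count is soft.** No test is named for mortality in the risk-ratio list, nor for satisfaction, which also appears under the process evaluation. Dropping satisfaction gives 1 − 0.95^13 = 49%. The three healthcare-use items have no clear direction of benefit, because the intervention includes community referral; without them a false benefit has a chance of at most 1 − 0.975^11 = 24%. These changes reduce the figures without removing the point.

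**Stronger readings that the article does not support.** A reader might infer that a false finding of benefit is likely. The 51% counts both directions and assumes independence; a false benefit passes 50% only at about 28 independent tests (ln 0.5/ln 0.975 = 27.4). A reader might also infer that the investigators intend to claim benefit from an isolated secondary result, or after a null primary result. No section says so, and the objective is worded as an examination.

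**Conclusion.** The point holds in a limited form. The article applies an unadjusted 5% level to about 14 secondary comparisons and an unstated number of subgroup tests, without ordering them or giving them formal supportive status. The primary analysis is sound in this respect.

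The size depends on the per-test reading of the rule, the count of 14, no true effect on any of these outcomes, and the assumed correlations. Even at a correlation of 0.8 the either-direction rate is four times the 5% that a single test carries. At a correlation of 0.7 the chance of a false benefit is 12%, against 2.5% for a single test. The sentence is worth changing, because the questions on safety, function and quality of life rest on these outcomes.

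**What to change.** Replace the closing sentence of {20a} with wording such as:

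*ED/AMAU length of stay is the only confirmatory test (two-sided 5%). Secondary outcomes and subgroups are supportive or exploratory and are reported as estimates with 95% confidence intervals, without claims of statistical significance; for each binary outcome one model is named as the reported result.*

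If a confirmatory claim on a secondary outcome is wanted, name a short ordered list and test it in sequence, only after the primary outcome is significant. If a separate analysis plan already does this, bring the two documents into line.

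The change takes a sentence or two and needs no additional patients or data. The small downside is that a lone secondary p < 0.05 could no longer be offered as proof of benefit.

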### Interim analyses {21b}

There is no plan for an interim analysis.

### Methods for additional analyses (e.g. subgroup analyses) {20b}

There will a subgroup analysis based on discharge location and Clinical Frailty Score [16].

Subgroup analysis exploring the subgroup of control participants who were seen by the OPTIMEND team will be carried out. OPTIMEND is a health and social care professional team who perform certain components of CGA but without specialist geriatric medicine input.

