CGA is acknowledged as the gold standard of care for the frail older person [5, 6]. Most studies that examine CGA agree that it consists of a medical, social, functional and psychological review and these constructs determine the overall health of an individual. A comprehensive multifaceted approach, thereby, grants the opportunity to create a synergistic management plan for patients with targeted interventions across these broad domains. A Cochrane review [6] has shown that the use of CGA confers quantifiable and reproducible benefits to the health and wellbeing of older people. The value of CGA in various settings and implementation stages has been established. CGA has been shown to potentially reduce mortality and increase home discharge when performed in dedicated geriatric wards as well as when delivered by mobile geriatric units [6]. It has also been investigated as a treatment model in the surgical inpatient unit setting for elective surgical oncology patients and for those recovering from hip fractures [7]. CGA has been shown to have variable outcome benefits in primary and long-term care settings [8]. A systematic review of five randomised controlled trials by Conroy and colleagues (2011) reported that there was no clear evidence of benefit for CGA interventions among older adults in the ED [9]. Mortality [RR 0.92 (95% CI 0.55–1.52)], readmissions [RR 0.95 (95% CI 0.83–1.08)], subsequent institutionalisation, functional ability, quality-of-life or cognition were not statistically significant in the intervention group. The studies primarily investigated single interventions which were heterogenous in nature [9].

The overall aim of this study is to examine the impact of multicomponent CGA on the quality, safety and cost-effectiveness of care in an undifferentiated population of frail older people with medical complaints who present to the ED and Acute Medical Assessment Unit.

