## Interventions

### Explanation for the choice of comparators {6b}

The comparison group will receive usual care as would be current practice in the ED or AMAU. Currently, there is no dedicated team to perform CGA in the ED and AMAU at UHL with ad hoc allied health assessment available only at the discretion of the referring ED doctor or medical team. This process of usual care will be continued during the study and will be documented.

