**Fig. 1 Fig1:**
[figure not shown]
Example template of recommended content for the schedule of enrolment, interventions, and assessments. Recommended content can be displayed using various schematic formats. See SPIRIT 2013 Explanation and Elaboration for examples from protocols. **List specific time points in this row. t1 Assessment. t2 Admission OR discharge. t3 30 day outcomes. t4 180 day outcomes

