### Concealment mechanism {16b}

Allocation will be concealed from participants and researchers until both consent has been obtained and baseline evaluations has been performed. After allocation is revealed, the intervention will be organised by the team.

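### Discharge location and OPTIMEND contact in controls are not baseline subgroups, so treatment comparisons built on them are not randomised and are open to bias

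*Protocol article*

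**What the plan says.** Under Methods for additional analyses {20b}, the protocol article names two subgroup factors: "There will a subgroup analysis based on discharge location and Clinical Frailty Score". It then adds: "Subgroup analysis exploring the subgroup of control participants who were seen by the OPTIMEND team will be carried out". The section describes OPTIMEND as a health and social care professional team that delivers some components of CGA without specialist geriatric medicine input.

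Four other places fix the timing and nature of these variables.

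- Outcomes {12}: the primary outcome is ED length of stay, "recorded as time of arrival at the ED until discharge from ED to home or admission to a ward". A parallel definition covers the Acute Medical Assessment Unit (AMAU).
- Fig. 1 legend: the order is "t1 Assessment. t2 Admission OR discharge".
- Concealment mechanism {16b}: "After allocation is revealed, the intervention will be organised by the team". Disposition therefore follows allocation.
- Background and rationale {6a}: "CGA has been shown to potentially reduce mortality and increase home discharge when performed in dedicated geriatric wards". This is inpatient evidence, but it shows that the article regards disposition as something CGA may change.

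On usual care, Explanation for the choice of comparators {6b} refers to "ad hoc allied health assessment available only at the discretion of the referring ED doctor or medical team". It does not mention OPTIMEND by name.

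**The concern.** A subgroup contrast inherits the protection of randomisation only if membership is fixed before allocation, or cannot be influenced by it. Two of the three named subgroups do not meet this condition.

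If CGA sends home some patients who would otherwise have been admitted, the home and ward groups hold different kinds of patient in the two arms. Comparing arms within either group then mixes any treatment effect with a difference in case mix. For length of stay the problem is sharper, because disposition is the event that ends the measured interval.

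The OPTIMEND subgroup has no counterpart in the intervention arm. Setting it against that arm compares everyone randomised to one side with a selected part of the other. A control who stays longer also has more opportunity to be seen, so selection may depend on the outcome itself.

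At stake is how the secondary results are read: who benefits from CGA, and whether geriatrician-led assessment adds anything to an allied-health team. Statistical methods {20a} applies a 5% significance level to all analyses, and {20b} adds no caution for these subgroups.

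**Working it through.** **The plan's own figure.** Inputs from Sample size {14}: mean 18.63 h, SD 19.91 h, intervention mean 9.31 h (difference 9.32 h), 90% power, two-sided 5%, 20% attrition. Normal approximation: n = 2 × [19.91 × (1.960 + 1.282) / 9.32]² ≈ 96 per arm; 96/0.8 = 120 per arm, 240 in total. The t-test version gives 97 per arm; 97 × 1.2 ≈ 117, 234 in total. The stated 236 lies between the two and is not in question here.

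**Assumptions for the illustration.** Only the mean and SD come from the article; all else is assumed.

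- Length of stay is log-normal and identical in both arms. σ² = ln[1 + (19.91/18.63)²] = 0.762, so σ = 0.873.
- A patient is admitted if a severity score, correlated ρ with log length of stay, exceeds the cut that gives admission proportion p.
- Control admission is 50% or 60%, CGA lowers it by 10 or 15 points, and ρ is 0.3 or 0.6.

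**Discharge location.** With z = Φ⁻¹(p):

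- mean stay if admitted = 18.63 × Φ(ρσ + z) / p
- mean stay if sent home = 18.63 × [1 − Φ(ρσ + z)] / (1 − p)

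Example with ρ = 0.6 and admission 50% in controls, 35% under CGA:

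- Controls: Φ(0.524) = 0.6998. Admitted 18.63 × 0.6998/0.50 = 26.07 h; home 18.63 × 0.3002/0.50 = 11.19 h.
- CGA: Φ(0.524 − 0.385) = 0.5550. Admitted 18.63 × 0.5550/0.35 = 29.54 h; home 18.63 × 0.4450/0.65 = 12.75 h.
- Overall CGA mean: 0.35 × 29.54 + 0.65 × 12.75 = 18.63 h, the same as in controls.

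Both strata show a longer stay under CGA although no patient's stay has changed. The full grid, as CGA minus control from unrounded means:

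| ρ | Admission, control → CGA | Home (h) | Admitted (h) |
|---|---|---|---|
| 0.3 | 50% → 40% | +0.64 | +0.97 |
| 0.3 | 50% → 35% | +0.96 | +1.52 |
| 0.3 | 60% → 50% | +0.66 | +0.84 |
| 0.3 | 60% → 45% | +0.98 | +1.31 |
| 0.6 | 50% → 40% | +1.03 | +2.18 |
| 0.6 | 50% → 35% | +1.57 | +3.47 |
| 0.6 | 60% → 50% | +1.01 | +1.81 |
| 0.6 | 60% → 45% | +1.52 | +2.84 |

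Simulation gave 0.7-1.6 h (home) and 0.9-3.4 h (admitted), which agrees apart from simulation error and the scenarios covered. If admission does not shift, or if ρ = 0, every entry is zero.

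**False significance.** In simulated trials of 118 per arm (Mann-Whitney, 2,000 trials per scenario, admission 60% → 50%), at least one stratum was significant in 10% of trials at ρ = 0.3 and 15% at ρ = 0.5. Two unbiased tests give 1 − 0.95² ≈ 10%. The whole-group test stayed at 4.3-5.4% across the discharge-location scenarios.

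**OPTIMEND.** Suppose that the comparison is the whole intervention arm against seen controls, and that contact depends only on staying long enough. With stay Y and an exponential wait of mean h, the mean stay of seen controls is E[Y(1 − e^(−Y/h))] / E[1 − e^(−Y/h)]. For h = 4 h this is 20.4 h; for h = 8 h it is 22.4 h. Against 18.63 h in the intervention arm, the false advantage is about 1.7 h and 3.8 h. It is zero if contact is unrelated to length of stay.

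**The case against.** Much can be said on the other side, and several points stand.

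- Section {20b} names no outcome for its subgroups. Length of stay is inferred because it is the primary outcome; 30-day or 6-month outcomes are also possible.
- Discharge location is not defined. Provisions for post-trial care {30} mentions discharge to the community or a nursing home, so a home/ward split is an inference.
- No comparator is given for the OPTIMEND subgroup. The wording also fits a description of what usual care contained, which would be harmless.
- A reader might infer from {6b} that OPTIMEND contact is at clinician discretion. That passage concerns ad hoc allied health assessment and does not name OPTIMEND. Nor does the article say when contact occurs, so some could precede allocation.
- The evidence that CGA increases home discharge is from inpatient settings, and the same section reports no clear benefit in the ED. Changing disposition is not a stated objective.
- These are additional analyses, and no decision rule depends on them.

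These points limit what can be claimed about size and certainty. They do not remove the structural problem: however discharge location is categorised, it is known only after allocation, and the OPTIMEND group exists in one arm only. An interaction test would not repair either.

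**Conclusion.** The concern holds in a conditional form: the comparisons are open to bias, not shown to be biased. For length of stay, bias arises if CGA shifts disposition and disposition is related to stay, or if OPTIMEND contact is related to stay. Under the stated assumptions the spurious differences are about 0.6-1.6 h (home), 0.8-3.5 h (admitted) and 1.7-3.8 h (against OPTIMEND-seen controls). All are illustrative, since the article gives no admission rates, waits or correlations. At the low end the false-positive rate is hardly distinguishable from that of two unbiased tests.

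Two stronger readings are tempting and not supported. One is that these analyses would reverse the sign of the result. That needs a true effect near zero: at the planned 50% reduction, halving the most biased CGA means above gives 12.75/2 = 6.4 h against 11.2 h (home) and 29.54/2 = 14.8 h against 26.1 h (admitted), still favouring the intervention. The other is that the trial's main conclusion is at risk. It is not: the primary comparison uses all randomised patients, and the sample size of 236 is untouched. This should be fixed, but it is not a fatal flaw.

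**What to change.** Amend section {20b} as follows.

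1. Remove discharge location as a subgroup. Report index-visit disposition by arm as an outcome or, if stay by destination is of interest, report cumulative incidence of discharge home and of ward admission as competing events in all randomised patients.
2. Restrict subgroup tests to variables fixed before randomisation, using a treatment-by-subgroup interaction. Clinical Frailty Score qualifies if it is scored at baseline; ED versus AMAU setting at randomisation is another candidate.
3. Report OPTIMEND contact among controls descriptively, as part of the content of usual care. Label it non-randomised and attach no treatment-effect claim.

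The cost is wording only. Disposition is already recorded at t2 in the Fig. 1 timeline, and the sample size does not change. What is given up is disposition-specific and SOLAR-versus-OPTIMEND estimates presented as treatment effects.
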